## Abstract

Physical activity is essential for the health and well-being of children and adolescents. However, those living with cancer often experience reduced physical activity levels, which negatively impact their functional capacity and health-related quality of life (HRQoL). In Ecuador, data from the National Institute of Statistics and Census (2021) reveal that 20% of children engage in less than one hour of physical activity per week, highlighting the need for targeted interventions. While previous studies demonstrate that supervised exercise programs can improve physical and psychosocial health outcomes in pediatric oncology patients, no evidence exists from Ecuador to assess the effects of such programs. This study will examine the impact of a structured physical activity program on the HRQoL of pediatric cancer patients in Quito, Ecuador. Using a case-control design, 90 participants will be randomized into two groups: an intervention group receiving a 10-week, supervised physical activity program and a control group with no exercise intervention and standard care, with additional follow-up if deemed necessary by the social worker. HRQoL surveys using a standardized instrument will be administered to all participants (those in the intervention group and those in the control group) at baseline, post intervention, and follow-up to assess changes over time. This research will address a critical public health gap by exploring how physical activity can mitigate the adverse effects of cancer treatment, improve physical and emotional health, and enhance the HRQoL in pediatric oncology patients. Findings will contribute valuable insights for integrating physical activity into pediatric oncology care in low- and middle-income countries.

## Introduction

Physical activity plays a critical role in the growth and overall well-being of children and adolescents (1). However, those living with cancer face significant barriers to maintaining adequate physical activity levels (1). Regular physical activity has been shown to yield numerous benefits, including improvements in health-related fitness, fatigue management, neurocognitive functioning, and psychosocial well-being (2). Despite these advantages, children undergoing cancer treatment often experience reduced levels of physical activity compared to their healthy peers, which may negatively impact their health-related quality of life (HRQoL) (19, 20).

In Ecuador, there is a notable gap in research examining the impact of physical activity on pediatric cancer patients. National statistics underscore the importance of addressing this issue, as in 2021 National Institute of Statistics and Census of Ecuador reported that 3.4 million children and adolescents aged 5–17 did not meet recommended physical activity levels (3). Additionally, 20% of children engage in less than an hour of physical activity per week (4). This lack of physical activity is even more pronounced among children with cancer. Studies have shown that children undergoing chemotherapy are not only less active than their healthy peers but also exhibit lower functional capacity and diminished HRQoL (19, 20).

Globally, pediatric cancer affects approximately 400,000 children and adolescents aged 0–19 annually, with nearly 30,000 cases occurring in Latin America and the Caribbean (5, 6). In Ecuador, an estimated 1,027 new cases of pediatric cancer are diagnosed each year, with 401 deaths reported in individuals under 20 years old (6). The most common cancers in this population include leukemia, lymphoma, and central nervous system tumors (6). While advancements in cancer treatment have improved survival rates in high-income countries, less than 30% of children in low- and middle-income countries achieve remission due to limited access to comprehensive care (6).

Cancer treatments such as chemotherapy, surgery, and radiotherapy can lead to adverse effects, including reduced muscle strength, lower bone density, and fatigue (7). Historically, children undergoing treatment were advised to rest extensively; however, evidence now suggests that physical inactivity exacerbates these conditions (7). For children with cancer, structured physical activity programs have been shown to help mitigate these adverse effects and restore compromised aspects of physical health and well-being (1, 7).

Both the World Health Organization (WHO) and the U.S. Department of Health and Human Services recommend that children and adolescents engage in at least 60 min of moderate to vigorous physical activity daily (8, 21). These guidelines emphasize aerobic, muscle-strengthening, and bone-strengthening activities tailored to the child's age and enjoyment levels (8). Nevertheless, studies indicate that children with cancer often struggle to meet these guidelines, further highlighting the importance of interventions aimed at promoting physical activity (9).

Research on physical activity interventions for pediatric oncology patients demonstrates significant benefits. For instance, a 16-week program led to improvements in physical health, emotional well-being, and overall HRQoL (10, 11). By the eighth week, participants also showed enhanced social functioning and reduced fatigue (10). Similarly, studies have reported improvements in psychosocial functioning, with marked differences in emotional health scores (11). These findings underscore the potential of physical activity as a complementary therapy to reduce the adverse effects of oncological treatments and enhance HRQoL during and after treatment (12).

Despite these promising outcomes, pediatric cancer patients in Ecuador face unique challenges that limit their participation in physical activity. This study will aim to address these challenges by assessing the impact of a structured physical activity program on the HRQoL of pediatric cancer patients in Quito, Ecuador. By focusing on a population often overlooked in public health research, this study seeks to provide evidence-based insights into the role of physical activity in supporting the holistic well-being of children living with cancer.

## Material and methods

### Design

This study is designed as a randomized controlled trial to investigate the impact of a structured exercise program on the HRQoL of pediatric cancer patients. A total of 90 participants will be recruited and randomly assigned to either the intervention group or the control group.

The intervention group will participate in a 10-week structured physical activity program consisting of 120 min of supervised exercise per week, led by a team of physiotherapists and physical activity professionals from Hospital Sociedad de Lucha Contra el Cáncer del Ecuador (SOLCA) Quito. Meanwhile, the control group will not participate in any organized physical activity program but will continue with their usual activities. As part of the evaluation process, two versions of the Pediatric Quality of Life Inventory (PedsQL) survey will be administered: one tailored for children aged 8–12 and another for adolescents aged 13–18. Both groups will complete their respective surveys at three time points—baseline (week 0), post intervention (week 11), and follow-up (week 24). This approach allows for the assessment of changes in HRQoL over time and enables comparative analysis between the two age groups.

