### Main outcome

This research focuses on assessing the HRQoL of pediatric cancer patients, emphasizing the relationship between structured exercise programs and improvements in well-being. HRQoL is defined, as per Dac and Abhishek, as the overall well-being of individuals, incorporating both positive and negative aspects of their lives at a specific point in time (13). Key dimensions include physical, mental, and spiritual health; relationships; education; sense of security; and general well-being (13).

To evaluate HRQoL, the study will use the PedsQL, specifically the PedsQL 3.0 Cancer Module, a validated instrument for pediatric cancer patients aged 2 to 18 years. Two age-appropriate versions will be administered, one for children aged 8–12 and another for adolescents aged 13- 18. This module comprises 20 questions addressing physical, emotional, and social functioning, as well as cancer treatment-related symptoms. Participants will self-report their responses using a four-point Likert scale, with options ranging from “never” (0) to “almost always” (4). For example: “In the past month, how often have you felt tired?”; “In the past month, how often have you experienced pain or discomfort?”.

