### Statistical analysis

The data from the PedsQL surveys will first undergo descriptive analysis by age group surveys for children and adolescents. Numerical variables will be summarized as mean and standard deviation for variables with a normal distribution or median and interquartile range for non-normally distributed variables. Categorical variables will be summarized as absolute and relative frequencies. This descriptive approach will provide an overview of the data and support subsequent analyses (see Supplementary Table 2 for details on variables and survey items).

To evaluate the primary research question regarding the impact of the physical activity program on HRQoL, a bivariate analysis will be conducted. The analysis will compare exposure to the physical activity program (intervention vs. control group) and the PedsQL survey scores at different time points (week 0, week 11, and week 24). For numerical variables with a normal distribution, the Student's t-test for independent samples will be used. For non-normally distributed variables, the Mann–Whitney *U* test will be applied. Additionally, to evaluate within-group changes over time (e.g., baseline vs. end of study), paired tests will be conducted using either the paired Student's t-test for normally distributed variables or the Wilcoxon signed-rank test for non-normally distributed variables.

An intention-to-treat analysis will be employed to ensure the robustness of the results and account for potential non-compliance or missing data. This approach will analyze participants based on their initial group assignment (intervention or control), regardless of adherence to the program or completion of all study components (22).

Statistical significance will be set at *p*-value < 0.05. All analyses will be performed using R Studio (R Project version 4.3.2).

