### Sample size calculation

The sample size calculation for this study was conducted considering a confidence level of 95%, a power of 80%, equal variances between groups, and a 1:1 ratio between sample sizes. The difference in means to be detected was set at 4.36, based on literature identifying this value as the minimum clinically significant difference (17). The common standard deviation was calculated at 11.26, using the formula for the standard error of measurement (SEM = 15 × √1−0.85), where the Cronbach's alpha reliability coefficient is 0.85. The formula for hypothesis testing by comparing means of independent groups was applied using the Epidat 4.2 program, resulting in a required sample size of 106 participants per group. To account for an estimated 20% loss to follow-up, the sample size was increased to 133 participants per group. However, due to budgetary limitations, the final study sample will consist of a total of 90 participants (approximately 45 per group). While this is lower than the 160 participants initially estimated through power calculations, this adaptation reflects real-world constraints commonly encountered in resource-limited settings. The study is therefore best positioned as a pilot randomized controlled trial, with the aim of generating preliminary data to inform future larger-scale interventions.

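### The Design section offers a comparison of children with adolescents that the Statistical analysis section does not plan and that 90 participants cannot support at a clinically relevant size

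*Protocol article*

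**What the plan says.** All references are to the protocol article.

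- **Design.** Two questionnaire versions are used, "one tailored for children aged 8–12 and another for adolescents aged 13–18", at weeks 0, 11 and 24. The section says that this "enables comparative analysis between the two age groups". It does not say whether scores or programme effects are to be compared.
- **Main outcome.** "Two age-appropriate versions will be administered" of one cancer module, described as having 20 questions. Nothing is said on whether scores from the two versions are equivalent.
- **Statistical analysis.** The only analysis assigned to age is a "descriptive analysis by age group surveys for children and adolescents". The inferential analyses are a t-test or Mann–Whitney test of intervention against control, and paired tests within groups. No arm-by-age contrast is named.
- **Sample size calculation.** "The difference in means to be detected was set at 4.36" points, with a common SD of 11.26. The requirement was 106 per group, or 133 after allowing for 20% loss. The trial will enrol 90 in total and is described as best seen as a pilot.
- **Limitations.** Reduced power for small effects is acknowledged, with no mention of age groups.

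**The concern.** The age comparison is stated as something the design delivers, so it is a positive claim and not a detail left for later. It can be read in two ways, and both have a problem.

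1. **Child scores against adolescent scores.** Age is not randomised, and every child answers one version while every adolescent answers the other. A raw difference in scores therefore mixes age with version.
2. **Programme effect in children against programme effect in adolescents.** This contrast is protected by randomisation, but it needs an arm-by-age estimate. None of the named tests provides one, and the sample was already too small for the overall effect.

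What is at stake is the reporting. The Discussion says the results may serve as a foundation for larger trials and inform policy. A finding about age based on this claim would carry far more uncertainty than the Design section suggests.

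**Working it through.** **Inputs from the Sample size calculation section.** Difference 4.36; SD 11.26; "a confidence level of 95%, a power of 80%, equal variances between groups, and a 1:1 ratio between sample sizes", read as two-sided 5%; 20% loss; 90 participants, about 45 per arm.

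**Assumption.** An even age split, since none is stated: 90 / 4 = 22.5 per arm per age group, and 22.5 × 0.8 = 18 after loss.

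**1. The plan's own figure.** n per group = 2 × [11.26 × (1.960 + 0.842) / 4.36]² = 104.7. The t-based calculation gives 106 (power 80.1%), as stated. With loss, 106 / 0.8 = 132.5, so 133. Both figures reproduce.

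**2. Overall power at the size enrolled (t-based).** About 44% with 45 per arm and 37% with 36 per arm.

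**3. Arm-by-age contrast.** This is the arm difference in children minus the arm difference in adolescents. It combines four cell means, so SE = SD × √(4 / n per cell).

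| | 22.5 per cell | 18 per cell |
|---|---|---|
| SE, SD 11.26 | 11.26 × √(4/22.5) = 4.75 | 11.26 × √(4/18) = 5.31 |
| 95% CI half-width | 9.4 | 10.6 |
| Power for a 4.36-point contrast | 15% | 13% |
| Contrast detectable with 80% power | 13.5 | 15.1 |

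The detectable contrast is 13.5 / 4.36 = 3.1 to 15.1 / 4.36 = 3.5 times the plan's minimum important difference. For 80% power at 4.36 points, n per cell = 4 × [11.26 × 2.802 / 4.36]², about 210, or 840 in total.

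**4. Sensitivity.**
- *SD.* The formula printed beside 11.26 gives 15 × √(1 − 0.85) = 5.81. At 5.81, power for the contrast is about 42% (35% after loss), and the detectable contrast is 6.9 (7.8) points. At SD 15, power is about 11%.
- *Age split.* At 30:70 with SD 11.26 and no loss, power falls to about 13%.
- *Baseline adjustment.* This is not in the plan. With an assumed correlation of 0.5 to 0.7, power without loss would be about 18% to 25% (normal approximation).

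Power for a 4.36-point contrast stays below 50% in every case.

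**5. If arms were tested separately within each age group.** The plan does not state this analysis. Power within one age group would be about 24.6% (20.4% after loss). With the same true 4.36-point effect in both, exactly one of the two tests would be significant with probability 2 × 0.246 × 0.754 = 37% (2 × 0.204 × 0.796 = 32% after loss).

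**The case against.** The strongest reply is that the article never promises to show a differential effect by age. Its only stated analysis by age is descriptive, its primary comparison is between arms, and it calls itself a pilot with reduced power. Much of this stands: reading the Design sentence as a claim about differential effect is an inference. But the pilot and power caveats do not mention age groups, and nothing limits the Design sentence to description.

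Some stronger readings are tempting, and the document does not support them:

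- *That the trial will test each age group separately and compare p-values.* No section plans this. The article does not say whether the between-arm tests pool the two surveys, so the 32% to 37% figure is only a warning about one possible use.
- *That the two versions are not comparable.* They are presented as versions of one module, and nothing shows non-equivalence. The issue affects only raw comparisons between ages; an arm comparison within an age group uses a single version.
- *That the interaction is the only randomised question about age.* The arm effect within each age group is also protected by randomisation. It is merely imprecise.
- *That randomisation is not stratified by age.* The article names the REDCap tool and neither states nor excludes strata. A condensed article may leave this to the full protocol.
- *That no age difference could be detected.* A contrast of about 13.5 points or more could be, at SD 11.26 with an even split and no loss.

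**Conclusion.** The point holds in limited form. The Design section claims an age-group comparison for which the Statistical analysis section has no inferential counterpart, and which 90 participants cannot support at a clinically relevant size. At SD 11.26 with an even age split, power for a 4.36-point contrast is 13% to 15%, and the interval around the contrast would be roughly ±9 to ±11 points. The figures rest on the assumed split and on an SD whose stated derivation does not reproduce. At the more favourable SD of 5.81 power is still only 35% to 42%, and uneven splits lower it. A raw comparison of child with adolescent scores cannot separate age from version unless equivalence is shown, which the article does not address. The primary comparison of intervention with control is not invalidated.

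**What to change.** - **Design:** remove the statement about comparing age groups, or restrict it to exploratory description.
- **Statistical analysis:** make the primary between-arm estimate a single pooled one, with age group as a factor. Age group coincides with version, so the factor absorbs a difference in level between versions. Pooling still assumes that a point means the same on both, and this should be stated.
- **Statistical analysis:** report any arm-by-age-group contrast only as an exploratory estimate with its 95% confidence interval. Make no separate significance claims by age group.
- **Optional:** stratify the REDCap randomisation by age group, if still feasible and not already done.

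The cost is a few sentences and one model term. Age is already collected and no extra participants are needed. The sponsor gives up a conclusion about age that the trial could not reliably reach.

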### Ethics

The study protocol has been reviewed and approved by the Cancer Committee and the Institutional Review Board (IRB) of the University of Minnesota and the Ethics Committee of the Universidad San Francisco de Quito (Quito, Ecuador) (ID: 2024-068M). The research will strictly adhere to the ethical principles outlined in the Declaration of Helsinki and comply with national and international guidelines for studies involving human participants. Written informed consent will be obtained from all the legal guardians, and assent will be sought from the children, as appropriate for their age and cognitive ability. The study is registered on ClinicalTrials.gov identifier NCT06813950.

### Study team

The study team will consist of a interdisciplinary group of professionals, including:
•A medical oncologist, responsible for overseeing the clinical care of participants and ensuring the safety of interventions.•A social worker, providing psychosocial support to participants and their families.•A physiotherapist, designing and supervising physical activity sessions.•A principal investigator, coordinating the study and ensuring compliance with the protocol.•Physical education professionals, implementing the exercise program and monitoring participant engagement.This diverse team will ensure a holistic approach to the intervention, combining expertise in clinical care, physical activity, and participant well-being (Supplementary Table S1).

### Main outcome

This research focuses on assessing the HRQoL of pediatric cancer patients, emphasizing the relationship between structured exercise programs and improvements in well-being. HRQoL is defined, as per Dac and Abhishek, as the overall well-being of individuals, incorporating both positive and negative aspects of their lives at a specific point in time (13). Key dimensions include physical, mental, and spiritual health; relationships; education; sense of security; and general well-being (13).

To evaluate HRQoL, the study will use the PedsQL, specifically the PedsQL 3.0 Cancer Module, a validated instrument for pediatric cancer patients aged 2 to 18 years. Two age-appropriate versions will be administered, one for children aged 8–12 and another for adolescents aged 13- 18. This module comprises 20 questions addressing physical, emotional, and social functioning, as well as cancer treatment-related symptoms. Participants will self-report their responses using a four-point Likert scale, with options ranging from “never” (0) to “almost always” (4). For example: “In the past month, how often have you felt tired?”; “In the past month, how often have you experienced pain or discomfort?”.

### Collection of demographic data

Demographic data will be collected during the enrollment phase by medical oncologists from both Hospital SOLCA Quito and Hospital Baca Ortiz. The variables collected will include:
•Age: Retrieved from medical records or, if unavailable, verified using the participant's identification document. The participant's age will be recorded based on the enrollment date documented in the consent and assent forms.•Sex: Recorded as indicated in the medical records.

### Collection of clinical data

Clinical data will be collected during the enrollment phase by medical oncologists at both recruitment sites. The variables include cancer type and treatment status. Cancer type will be classified according to the International Classification of Diseases, 10th Revision (ICD-10). Treatment status will be determined through a review of medical records, with participants categorized as either “regular follow-up”, referring to patients in post-treatment monitoring, or “undergoing treatment”, referring to patients actively receiving oncological therapy. This information will be used to apply the inclusion and exclusion criteria.

The body weight of the participants will be measured via an electronic scale (with an accuracy of 0.1 kg), whereas height will be determined via a portable height rod with an accuracy of 0.1 cm. The calculation of body mass index involves dividing an individual's body weight (measured in kilograms) by the square of their height (measured in meters). Additionally, the body mass index *z* score is determined via the age-specific and sex-specific thresholds established by the WHO (21).

